## Abstract

**Background:**

A subset of patients with schizophrenia do not respond sufficiently to conventional antipsychotic treatment and often have a more complex clinical course, including high rates of sleep disturbances, which can contribute to further worsening of symptoms. However, sleep disturbances are often overlooked in clinical psychiatric settings, and non-pharmacological treatment options are not initiated. Cognitive behavioral therapy for insomnia (CBT-I) has been shown to effectively ameliorate sleep disturbances in schizophrenia but is yet to be assessed in treatment-resistant schizophrenia. In the present study, we aim to investigate the efficacy of CBT-I versus standard cognitive behavioral therapy (CBT), an active control intervention.

**Methods:**

Sixty patients diagnosed with treatment-resistant schizophrenia and comorbid sleep disturbance will be included in this randomized intervention study. Included patients will be randomized to 8–10 sessions of psychotherapy with either CBT-I (active intervention) or regular CBT (active control) following baseline. At baseline and 12-week follow-up, patients will be assessed with clinical interviews (Positive and Negative Syndrome Scale), self-reported measures (e.g., Insomnia Severity Index), and polysomnography. The 24-week follow-up will include the same assessments apart from polysomnography. The active intervention group will receive an individual course of treatment with CBT-I focused on the patients’ sleep patterns, while the active control group will receive an individual course of treatment with standard cognitive behavioral therapy (CBT) focused on patients’ psychopathology. It is hypothesized that while both groups will show improvements on central outcome measures, CBT-I will show greater improvements in sleep disturbances. Further, it is hypothesized that the improvement in sleep disturbances will correlate with an improvement in positive symptoms. Lastly, it is anticipated that the CBT-I group will show objective improvements in sleep architecture, such as sleep latency, wake after sleep onset, sleep efficiency, and total sleep time, compared to the CBT group.

**Discussion:**

Should CBT-I prove efficacious in improving sleep disturbances in treatment-resistant schizophrenia, it would provide an avenue for a cost-beneficial, short-term, and implementable non-pharmacological treatment of a severe comorbidity in complex schizophrenia patients. Potential issues pertaining to the completion of the study are discussed.

**Trial registration:**

ClinicalTrials.gov NCT06749444. Registered on December 27, 2024.

## Administrative information

Note: the numbers in curly brackets in this protocol refer to SPIRIT checklist item numbers. The order of the items has been modified to group similar items (see http://www.equator-network.org/reporting-guidelines/spirit-2013-statement-defining-standard-protocol-items-for-clinical-trials/).

Role of sponsor {5c}	The sponsor’s role in study is to contribute to the analysis and interpretation of data as well as writing and submitting papers for publication. However, the sponsor will not have ultimate authority over any of these activities. The funding bodies have had no influence on any aspect of the study.

## Introduction

### Background and rationale {6a}

Sleep is essential to physical and mental health [1] and is often disrupted in people with schizophrenia and can be observed leading up to first-episode psychosis [2], making sleep disturbances a comorbidity that permeates the course of illness. Up to 80% of schizophrenia patients experience insomnia-related symptoms, whereas 30–40% meet the criteria of clinical insomnia [3, 4]. Sleep disturbances are prevalent, but clinically often-overlooked comorbidity that is linked to more severe symptoms and worse clinical prognosis [2].

Schizophrenia can be a debilitating psychiatric disorder characterized by symptoms, such as cognitive impairments, hallucinations, delusions, inadequate affect, and lack of initiative and motivation [5]. Antipsychotic medication improves psychotic symptoms in most patients, but 30–40% do not experience sufficient, if any, symptom reduction despite treatment [6]. These patients are defined as treatment-resistant schizophrenia (TRS) and are characterized by complicated pharmacological treatment and resistant psychopathology [7], which is further exacerbated by the presence of a comorbid sleep disturbance.

Cognitive Behavioral Therapy (CBT) is the first-line treatment for a range of psychiatric illnesses and is generally an effective treatment option for most assessed conditions [8]. Traditional second-wave Beckian CBT generally results in small, but significant effects on symptoms in the treatment of schizophrenia, proving most effective in treating positive symptoms, while largely ineffective in treating negative symptoms [9]. Besides pharmacological treatment of sleep disturbances in patients with schizophrenia, the last number of years has brought a rise in popularity of interventions based on principles from CBT.

*Cognitive behavioral therapy for insomnia* (CBT-I), a niche branch of broader CBT, offers a promising treatment of sleep disturbances that appear comorbidly with another psychiatric illness that is efficacious in addition to being cost-effective compared to pharmacotherapy and easy to implement [10]. CBT-I is a multi-component treatment comprised mainly of sleep restriction therapy (SRT), stimulus control therapy (SCT), cognitive therapy, and sleep hygiene psychoeducation [11, 12]. These components address the restructuring of dysfunctional assumptions about sleep and insomnia, rumination and worry, behaviors pertaining to falling asleep and waking up, and elevation of daytime activity levels [2]. CBT-I has been efficacious in treating chronic insomnia alone [13] and comorbid insomnia in depression [14] and anxiety [15]. CBT-I has also been used to treat insomnia in schizophrenia [2, 16–20]. Furthermore, CBT-I has been shown to produce greater and more lasting effects than common pharmacotherapy for insomnia [21] However, to our knowledge, CBT-I has not previously been rigorously investigated in TRS where pharmaceutical interventions are insufficient.

Several studies have found a positive relationship between insomnia and paranoid thoughts [22, 23]. The causality remains largely unknown, but it is most likely a circular, self-perpetuating relationship. Insomnia, anxiety, and paranoia may exacerbate each other, since both insomnia and paranoia are closely linked with negative affect, such as depression, anxiety, and rumination [22, 23]. A recent meta- analysis showed that insomnia was present in 50% of patients with schizophrenia and that disruption of sleep was a significant predictor of both onset and persistence of psychotic symptoms [24]. This meta-analysis showed that most patients were motivated for treatment and the intervention studies reported large effect size improvements in sleep and more modest, although still significant improvements in psychotic symptoms [24].

One of the best validated self-report measures of sleep and circadian disorders is the *Insomnia Severity Index* (ISI). This instrument was developed by comparing ISI with data from sleep journals and polysomnography (PSG) and comparing self-report ISI with peer-report ISI obtained from clinicians and relatives. ISI was able to detect changes in the perceived level of insomnia and can be used as a screening tool as well as an outcome measure [25]. ISI has recently been validated in a Danish context in a somatic outpatient clinic, where ISI-DK showed good reliability and validity [26].

PSG is an objective measure of sleep disturbances and is considered the golden standard of sleep assessment. Sleep research has discovered disorder-specific and transdiagnostic patterns and mechanisms, which implies that sleep disturbances are present comorbidly in many mental disorders leading to impairment in several areas [27]. Insomnia is characterized as difficulties falling and staying asleep with repeated awakenings or sleep that is perceived as nonrestorative or of poor quality [28]. Abnormalities in the structure of sleep seem to be an inherent part of schizophrenia, which is supported by a recent meta-analysis of PSG studies, which found sleep continuity and depth to be fundamentally altered in schizophrenia [27].

Likewise, deficits in sleep spindles and increased sleep latency have been observed in schizophrenia patients compared to non-clinical populations [2]. Lower sleep efficiency, despite longer total time asleep, more nightly awakenings, and a significantly higher score on *Pittsburgh Sleep Quality Index* (PSQI), reflecting worse subjective sleep quality, has also been demonstrated [29].

Despite the well-documented association between schizophrenia and insomnia in the existing literature, there is currently a gap in knowledge regarding nonpharmacological treatment options for sleep disturbances in TRS. Patients suffering from TRS are a heterogeneous group burdened by symptoms and significant side effects from the pharmacological treatment. We aim to investigate whether CBT-I is a useful nonpharmacological treatment option for TRS patients with sleep disturbances.

### Objectives {7}

Using a randomized controlled design, the project aims to investigate whether CBT-I can significantly lessen the burden of the disrupted sleep in patients with TRS and by proxy lead to a decrease in psychotic symptoms and increased quality of life. We hypothesize:CBT-I group will show greater improvements on *Insomnia Severity* Index (ISI) compared to active control group (primary hypothesis);CBT-I group will show greater improvements on *Positive and Negative Syndrome Scale* (PANSS) compared to active control group;The improvement in sleep disturbances will correlate with an improvement in positive symptoms as measured by PANSS;CBT-I group will show objective improvement in sleep architecture on polysomnography (PSG) as measured by a decrease in sleep latency (SL) and wake after sleep onset (WASO), and an increase in sleep efficiency (SE) and total sleep time (TST) compared to the active control group.

### Trial design {8}

This is a 12-week non-blinded randomized controlled trial (RCT) with a superiority framework. Patients will be randomized 1:1 using a block randomization regimen with variable block sizes (2, 4, and 6), which is done to achieve equal sample size in different groups over time [30]. For a flowchart of the trial, see Fig. 1.

**Fig. 1 Fig1:**
[figure not shown]
Flowchart of the COSTS trial

## Methods: participants, interventions, and outcomes

### Study setting {9}

The study will be conducted at the Unit for Complex Schizophrenia (UCS) at Mental Health Centre Glostrup, which is a university hospital located in Copenhagen, Denmark. UCS is a specialized psychiatric out-patient clinic, which has a steady referral of patients from the entire Capital Region for second opinions and complex treatments and has several active research projects on schizophrenia, including TRS.

### Eligibility criteria {10}

Patients with schizophrenia or other non-organic, chronic psychoses with a history of treatment-resistance can be included. In this project, we operationalize TRS as patients having positive symptoms that negatively influence their everyday function while receiving adequate psychopharmacological treatment. In addition, most of these patients will fulfill the strict definition of treatment-resistance (TRRIP-guidelines) [31], which states that participants have tried at least two antipsychotic drugs in sufficient dosage (equivalent to ≥ 600 mg chlorpromazine or half the dose of the maximum licensed dose) for sufficient time (≥ 6 weeks) without sufficient improvement in symptoms (moderate level of residual symptoms). Sleep disturbances are defined as sleeping difficulties pertaining to falling and staying asleep lasting ≥ 3 months [32] and a score of ≥ 15 on ISI [20]. Patients referred to UCS and fulfilling inclusion criteria will be offered to participate.Inclusion criteria:Diagnosed with ICD-10 schizophrenia (F20.x), chronic paranoid psychoses (F22), schizoaffective psychoses (F25.x), or other non-organic psychoses (F28–29)Ongoing positive symptoms equivalent to a score of at least 4 on PANSS positive item 1, 2, or 3 despite antipsychotic treatment at a sufficient doseSleep disturbance (duration ≥ 3 months and ISI score ≥ 15)Stable pharmacological treatment for ≥ 1 monthAge 18–64 yearsLegally competentExclusion criteria:Admission to a psychiatric ward within the last 6 months that lasted > 1 week OR resulted in significant changes to the pharmacological treatmentSubstance abuse to a degree that could interfere with adherence to and compliance with interventionDiagnosis of sleep apnea and usage of CPAP

### Who will take informed consent? {26a}

Prior to obtaining informed consent, the participant will be thoroughly informed about the research project and their rights as research participants in both verbal and written form, including information about randomization, the different interventions, and pre- and post-intervention assessments. The patient will also be informed about the intent to videotape one therapy session to ensure treatment fidelity as well as the baseline and follow-up assessment of psychopathology. After receiving the information, the patient will have a relevant consideration period of at least 24 h before the consent is obtained.

### Additional consent provisions for collection and use of participant data and biological specimens {26b}

Not applicable, no ancillary studies planned.

## Interventions

### Explanation for the choice of comparators {6b}

To test the efficacy of CBT-I, we compare it to regular CBT with a focus on patients’ psychopathology. CBT in general is an evidence-based treatment for treating several types of symptoms in a long range of psychiatric illnesses [8], including schizophrenia [9, 33–35]. In Denmark, CBT is recommended as a first choice of psychotherapeutic intervention for schizophrenia by the Danish Health Authority [36]. No significant difference in RCTs has been found between CBT and other psychotherapies in patients with schizophrenia; however, patients receiving CBT were more satisfied with the intervention, as measured by adherence to treatment [37]. There is generally a lack of evidence of efficacy for other psychotherapeutic interventions in schizophrenia, making CBT the most obvious choice of comparison for CBT-I. CBT-I has also shown to be effective in treating sleep disturbances in a schizophrenia population [2, 16–18] as well as in other psychiatric illnesses [14, 15]. CBT-I is the first-line intervention for insomnia issues across conditions. Therefore, it seems appropriate to compare CBT-I to CBT.

In pharmacological research, the preferred option for trials with a superiority design is to use active control in lieu of placebo control [38]. Meanwhile, authors of a recent review agree that all trial designs are relevant to psychiatric research [39].

Active control groups are often used in RCTs in mental disorders research, and a recent meta-analysis found that groups receiving active control treatment showed a small improvement over those receiving placebo treatment, although this was not found in the trials on schizophrenia included in the meta-analysis [40]. In psychotherapy research, the evidence for active control over placebo control is murky. Expectation effects in psychological interventions are only partly eliminated by an active control group [41]. However, we address expectancy and placebo effects by changing only the focus of the intervention in each group, while using the same therapeutic techniques. Furthermore, by offering two evidence-based interventions and presenting both as such, the expectancy effects are mitigated.

### Intervention description {11a}

Included patients will be randomized 1:1 to CBT-I with a specific focus on sleep or regular CBT with a specific focus on patients’ psychopathology and related difficulties. The interventions are delivered by two different psychologists with similar experience in the field.

Patients randomized to the CBT-I arm will receive a manualized intervention, specifically adapted for individuals with severe mental illness and sleep disturbances. The intervention is delivered individually over 8–10 sessions at UCS, scheduled approximately once per week across a 12-week period. The duration of sessions varies according to the treatment phase:Session 1 (Initial assessment): 60–120 minSession 2 (Treatment initiation): 60–120 minSessions 3–8 (Titration and relapse prevention): 45–60 min each

The extended duration of the first two sessions is necessary to allow for comprehensive assessment, individualized treatment planning, and thorough patient education.

The treatment protocol follows a Danish CBT-I manual developed for the COSTS project, which follows the general structure of previous manuals [42]. The first session includes a comprehensive assessment of sleep problems, confirmation of inclusion criteria, and introduction to the sleep diary, which patients are instructed to complete daily throughout the intervention. The sleep diary is used both for baseline assessment (between the first and second session) and as an ongoing tool to guide individualized treatment adjustments.

Core components of the intervention include:SRT: Based on the patient’s average TST from the sleep diary, an initial sleep window is set, with a minimum time in bed (TIB) of 5 h. Bedtime and rise time are fixed to strengthen circadian rhythms. Each week, the sleep window is titrated according to SE: if SE ≥ 85%, TIB is increased by 15 min; if SE is 80–84%, TIB is unchanged; if SE ≤ 79%, TIB is reduced by 15 min. Napping is discouraged throughout the intervention.SCT: Patients are instructed to go to bed only when sleepy, use the bed only for sleep and intimacy, leave the bed if unable to sleep after approximately 20 min, and maintain a consistent wake time regardless of sleep duration.Cognitive restructuring: The intervention targets unhelpful beliefs and worries about sleep, using cognitive techniques to challenge and modify maladaptive thoughts.Sleep hygiene and psychoeducation: Patients receive education on factors affecting sleep (e.g., caffeine, light, exercise), and are encouraged to optimize their sleep environment and routines.Relapse prevention: The final sessions focus on consolidating gains and developing strategies to prevent relapse.

The therapist follows a structured session plan, and adherence to the manual is monitored through continuous supervision by a senior clinical psychologist. The intervention is designed to be reproducible and evidence-based, following current recommendations for CBT-I [43].

The regular CBT intervention is delivered in a format identical to CBT-I. The structure, frequency, and duration of sessions are matched across both arms.

The primary difference is the therapeutic focus: regular CBT targets the participant’s psychopathology and related functional challenges, rather than sleep. Core components include psychoeducation, cognitive restructuring, behavioral experiments, coping skills training, and relapse prevention, with content individualized according to the participant’s needs.

Participants in the regular CBT arm complete a symptom log analogous to the sleep diary used in CBT-I, focusing on relevant psychiatric symptoms and coping behaviors. This log is reviewed in each session and guides the therapeutic process. This approach ensures both groups receive equivalent structure and intensity, with the main distinction being the content and focus of the intervention.

### Criteria for discontinuing or modifying allocated interventions {11b}

The psychotherapeutic intervention in both groups will be adjusted continuously for each trial participant given the individual nature. In the unlikely event that either intervention should result in a worsening of the psychotic symptoms, both the participant and the clinician providing the intervention can decide to discontinue the intervention, ideally in a way resembling shared decision-making.

Furthermore, 2 untimely cancelations or failures to appear in a row are considered non-compliance with the treatment, and the participant is excluded from the study.

Lastly, a change in a participant’s psychopathology which results in either substantial changes in antipsychotic medication or admittance lasting ≥ 7 days will result in exclusion from the study as per the exclusion criteria.

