### Relevant concomitant care permitted or prohibited during the trial {11d}

Patients will continue their regular psychopharmacological treatment and attend visits with their regular care team at the referring outpatient clinic. Substantial changes in antipsychotic medication or hospital admittance lasting ≥ 7 days will result in exclusion from the study.

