### Plans to promote participant retention and complete follow-up {18b}

Longitudinal follow-up data are important in clinical trials [57, 58]. Generally, issues with the collection of follow-up data can be summed up in the following categories: (1) unable to contact, (2) unable to complete, (3) refusing, and (4) unable to locate [57]. The loss of follow-up data due to subject attrition is a frequent cause of loss of statistical power or increased risk of bias, which minimizes the generalizability and validity of a clinical trial [57, 59]. Consequently, a robust plan for obtaining follow-up data is important. At the initial assessment, we focus on building rapport and positive interactions between participants and clinicians. This fosters participants’ commitment to both the project and staff [57]. We will build rapport through genuine interest in participants’ issues, history, and potential questions regarding project participation. Prospective participants are informed about the project’s goals, the importance of completing participation, and the personal benefits of participation. These strategies may raise the level of adherence throughout our study [59]. Obtaining accurate personal and demographic data is important in locating and contacting participants during the participation period. Furthermore, at the initial assessment, we will also schedule approximate dates for gathering follow-up data. Having scheduled appointments should increase the likelihood that participants will attend both follow-up sessions. Likewise, after participants have been assigned to a treatment group, the therapist in each group will send written reminders the day before each scheduled therapy session. A strong and continuous focus on overcoming these barriers should maximize the number of participants that complete the follow-up assessments.

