A core characteristic of clinical insomnia is that the affected person engages in compensatory strategies, for example, extension of total time spent in bed, withdrawal from occupational or private commitments, and/or inappropriate use of substances (illicit or otherwise) to either stay awake or fall asleep. In the CBT-I intervention, we employ SRT by restricting participants’ sleep opportunity (the time they are allowed to be in bed) for a period. We wish to inhibit the compensatory strategies that participants engage in, which perpetuate their sleep disturbances. However, we need to be careful in applying this therapeutic tool, since sleep deprivation is a factor in triggering and perpetuating psychosis. By using sleep restriction, we are, in a sense, lowering participants’ psychosis threshold, which is potentially problematic if it is not done in a controlled manner. To mitigate this risk, we have decided to not restrict below 5 h to prevent the worst sleep deprivation [42]. Furthermore, participants are seen by the therapist weekly, where they systematically assess the effect of SRT and any potential recurrence of psychotic symptoms. This enables the therapist and participant to collaborate on how to manage psychotic symptoms and when to potentially terminate the intervention. By taking these preventative steps, we want to ameliorate the potential adverse outcomes of CBT-I.

It can be challenging to adhere to a psychotherapeutic intervention, especially for people who meet the criteria for severe psychiatric disorders. Efficient psychotherapy requires sustained commitment, concentration, and a willingness to restructure thoughts and behaviors. Non-adherence is a potential pitfall, which makes the initial motivational work and sustained focus on maintaining motivation an important factor for success. During the initial contact, we will thoroughly explain the rationale and mechanisms of the interventions to enhance transparency and participants’ understanding. We have allocated a significant amount of time in the intervention manuals for motivational work, which we will tailor for each participant based on their specific situation. Throughout treatment, the therapist will routinely monitor each participant’s progress and provide support to keep motivation high. Furthermore, the procedures laid out in the intervention manuals require that time is allocated to refresh the rationale and mechanisms throughout the sessions.

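### Missed sessions, substantial antipsychotic changes and admissions of 7 days or more remove randomised patients from the study, not only from therapy, so follow-up is lost in a way linked to outcome

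*Protocol article*

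**What the plan says.** The section on discontinuing or modifying interventions {11b} treats three situations differently.

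- **Worsening psychotic symptoms.** Participant and clinician "can decide to discontinue the intervention, ideally in a way resembling shared decision-making". Only therapy ends.
- **Missed sessions.** "2 untimely cancelations or failures to appear in a row are considered non-compliance with the treatment, and the participant is excluded from the study".
- **Relapse-type events.** A change in psychopathology that leads to "substantial changes in antipsychotic medication or admittance lasting ≥ 7 days will result in exclusion from the study as per the exclusion criteria".

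The concomitant care section {11d} repeats the last rule without requiring a preceding change in psychopathology: "Substantial changes in antipsychotic medication or hospital admittance lasting ≥ 7 days will result in exclusion from the study".

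Four other sections bear on this:

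- Outcomes {12} are measured at baseline, 12 weeks and 24 weeks only. PSG is not repeated at 24 weeks.
- The missing-data section {20c} limits the analysis population to patients with four completed sessions, and names intention-to-treat analyses with last observation carried forward (LOCF).
- The retention section {18b} warns: "The loss of follow-up data due to subject attrition is a frequent cause of loss of statistical power or increased risk of bias".
- The eligibility criteria {10} contain an admission criterion, but it concerns the 6 months before entry and an admission of more than one week.

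**The concern.** Non-attendance, relapse with admission and a substantial antipsychotic change are part of the illness course, and possibly of the response to therapy. If they end study participation, the missing outcomes are not a random subset. The loss may also differ by arm. The Discussion notes that "sleep deprivation is a factor in triggering and perpetuating psychosis" and accepts that sleep restriction, used only in the CBT-I arm, could lower the threshold for psychosis.

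At stake is the comparison of ISI, and of PANSS and functioning even more directly, because the patients removed for relapse are those in whom PANSS would be expected to show deterioration. The rule also produces the attrition that {18b} sets out to avoid, and it sits badly with the intention-to-treat label in {20c}. A later analysis plan cannot repair this, since it cannot recover outcomes that were never collected.

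**Working it through.** **1. Does exclusion mean leaving the study?** {11b} uses one expression for ending therapy and another for ending study participation, within the same section. {11d} uses the second again. Nothing in the article provides for assessment at week 12 or 24 after exclusion. The plain reading is that follow-up stops, although no sentence says so outright.

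**2. What happens to an excluded patient's data?** From {12} and {20c}:

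- Excluded before four sessions: outside the analysis population.
- Excluded after four sessions but before week 12: the only planned value is baseline, so LOCF records a change of zero.
- Excluded after the week-12 visit: the primary outcome is kept, and the 24-week value is the week-12 value carried forward.

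**3. The plan's own figures {14}.** The inputs are 24 per group, 4 ISI points, 80% power and alpha 0.05. No SD is given. Solving two-sided for it:

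SD = 4 / [(1.960 + 0.842) × √(2/24)] = 4.95 (normal approximation), or 4.84 with the t distribution.

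The total of 60 equals 48 × 1.25. Allowing for 25% loss by division gives 48 / 0.75 = 64. That discrepancy is a separate matter, and nothing here depends on it.

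**4. How far can the estimate move?** Let r be the mean improvement in retained patients, w the mean change in excluded patients and e the share excluded before week 12.

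- All randomised: (1 − e)·r + e·w in each arm
- Retained only: r in each arm
- LOCF: (1 − e)·r in each arm

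All inputs below are assumptions. The shares average 25%, as if the whole expected attrition came from these rules, so they lie at the high end. Differences are CBT-I minus CBT; positive favours CBT-I.

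| e, CBT-I v CBT | r, CBT-I v CBT | All randomised, w = 0 / −2 / −4 | Retained only | LOCF |
|---|---|---|---|---|
| 25% v 25% | 8 v 4 | 3.0 / 3.0 / 3.0 | 4.0 | 3.0 |
| 30% v 20% | 8 v 4 | 2.4 / 2.2 / 2.0 | 4.0 | 2.4 |
| 35% v 15% | 8 v 4 | 1.8 / 1.4 / 1.0 | 4.0 | 1.8 |
| 20% v 30% | 8 v 4 | 3.6 / 3.8 / 4.0 | 4.0 | 3.6 |
| 35% v 15% | 6 v 6 | −1.2 / −1.6 / −2.0 | 0 | −1.2 |

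Example, third row with w = −4: (0.65 × 8 − 0.35 × 4) − (0.85 × 4 − 0.15 × 4) = 3.8 − 2.8 = 1.0. LOCF gives 5.2 − 3.4 = 1.8.

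LOCF is too favourable to CBT-I when more patients who worsen are lost from that arm (1.8 against 1.0). It is too unfavourable when more are lost from the control arm (3.6 against 4.0). In the last row a true disadvantage of 2.0 points shows as none among retained patients.

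**5. Power.** At SD 4.84 and a 4-point effect (t-test), 24 per arm gives 80%, 30 per arm 88%, and 22.5 per arm (60 × 0.75 = 45 patients) 77%. The gain from full follow-up is not assured, because adding patients off therapy may shrink the effect. At 3.0 points (first row) and 30 per arm, the noncentrality is 3 / (4.84 × √(2/30)) = 2.40 and power about 66%. The argument for follow-up is bias, not power.

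**The case against.** The strongest reply has four parts.

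- **The article is a condensed protocol.** The full document may provide for follow-up after exclusion. But the rule is stated here, in wording that the same section distinguishes from stopping therapy. If the full protocol provides for follow-up, this wording still needs correcting.
- **LOCF keeps some excluded patients in the analysis.** This stands for those with four sessions. It would be wrong to say that only stable attenders are compared. In the 30% v 20% row, LOCF (2.4) lies close to the all-randomised value (2.0 to 2.4).
- **The direction is open.** A reader might infer that CBT-I will look better than it is, or simulate loss in one arm and quote an inflated false-positive rate. The rules apply to both arms, and LOCF can turn the sign. With a share e lost from the CBT-I arm only, a true mean improvement m in both arms, and retained patients s points above m, the LOCF bias is (1 − e)(m + s) − m. At assumed e = 0.20 and s = 0.8 this is 0.64 − 0.2m, which runs against CBT-I once m exceeds 3.2 points. The article expects improvement in both arms.
- **Harm is not necessarily hidden.** Numbers and reasons for exclusion by arm could still be reported; the article neither promises this nor rules it out. Worsening symptoms alone lead to stopping therapy, not to exclusion. What is lost is measurement on the outcome scales after exclusion.

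Nor can one say that these exclusions come on top of the 25% attrition: {14} does not state what that figure contains. Finally, the tension with intention to treat arises partly from the four-session population, a separate matter.

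**Conclusion.** The point holds in this form. {11b} and {11d} as written end study participation for events that depend on adherence and clinical course and that may differ by arm. Outcomes after exclusion go unmeasured, and this conflicts with the retention aim in {18b} and the intention-to-treat analyses in {20c}.

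The article determines neither the direction nor the size of the bias. In the 8 v 4 illustrations, a retained-only comparison overstates the all-randomised difference by 0 to 3.0 points, and LOCF departs from it by between −0.4 and +0.8. These figures rest on assumed means and exclusion shares, and on all exclusions falling before week 12. The conclusion itself rests only on the plain meaning of the wording and the three assessment times. A claim that the trial would conceal harm or favour CBT-I goes further than the documents allow.

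**What to change.** In {11b} and {11d}, separate stopping therapy from leaving the study. Leave the clinical consequence for therapy as it is, and add that, whatever is decided about therapy, the patient remains in the trial, the event and its date are recorded, and the 12- and 24-week assessments are still sought unless consent is withdrawn. In {20c}, state that these patients are analysed in their randomised arm. Report by arm the admissions of 7 days or more, substantial antipsychotic changes, non-attendance and therapy terminations.

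Two inconsistencies must also be reconciled. {11b} appeals to the exclusion criteria, but {10} gives a pre-entry criterion with a threshold of more than one week, which an admission of exactly 7 days does not meet. And {11b} ties the medication and admission rule to a change in psychopathology, while {11d} does not.

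The cost is a short amendment, some effort to reach patients who have stopped therapy, and an estimate that includes patients off therapy. Approximate follow-up dates are already set at the initial assessment {18b}. With 5 of 60 patients included by 12 January 2026, the change would cover nearly the whole sample.
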